## Methods/Design

### Overview and hypotheses

Pregnant women or new mothers within one month of delivery who reside in one of six urban neighborhoods in Hartford, CT and were recruited into the NFN program were invited to participate in ECHO. These six neighborhoods were chosen because they are served by a Brighter Future Family (BFF) Center that is linked to the Nurturing Families Network home visitation program. Brighter Future Family Centers provide early childhood education programs and parenting classes designed to improve parents’ knowledge of child development and nurturing skills, support in earning a high school degree, understanding and speaking English, computer use and financial literacy and family play groups. Centers also provide information to parents about other community, city, state and national resources that might help them.

The six Brighter Future Family (BFF) Centers in Hartford, Connecticut and their NFN programs were paired by neighborhood socioeconomic and racial/ethnic characteristics (Table 1) and were randomly assigned to receive either the standard NFN home visitation program (n = 3) or the enhanced NFN home visitation program (NFN+, n = 3). The goal was to recruit 60 mothers and their newborns (10 from each BFF Center and its corresponding neighborhood) for a total of 30 mother/newborn dyads from an intervention BFF Center and its neighborhood and 30 dyads from a control BFF Center and its neighborhood. All dyads received the standard NFN curriculum using PAT and Partners curricula with weekly home visits. In addition, the NFN+ dyads received an enhanced curriculum in the areas of goal-setting, problem-solving, stimulus control and skill-building related to nutrition, physical activity, cues, and routines as well as enhanced neighborhood community services including coupons for Farmer’s Markets and grocery stores, cooking classes, and exercise classes.

**Table 1 Tab1:** Demographics of neighborhood pairs selected for randomization^a^

Neighborhood pair	1	2	3
Average family income	$28,191	$46,730	$33,697
Poverty rate^b^	42 %	14 %	34 %
Number of births (2010)	466	222	311
Total population (2010)	19,655	20,308	15,512
% Hispanic	50 %	32 %	41 %
% Black	32 %	45 %	44 %

^a^
http://www.hartfordinfo.org/Snapshots/neighborhood. Last accessed May 10, 2015

^b^City of Hartford Department of Health and Human Services. *A Community Health Needs Assessment.* Hartford, CT: City of Hartford Department of Health and Human Services;2012

We hypothesized that at 6 and 12 months, as compared to NFN infants, NFN+ infants would have been breastfed longer and more often exclusively, would drink less sugar-sweetened beverages/juice, would have begun to ingest solids at an older age, and would sleep more hours/day, have more established sleep/wake routines, greater soothability and have fewer hours of television viewing/day. Secondary hypotheses of the study included that at 6 and 12 months, as compared to NFN families, NFN+ families would purchase, cook and serve more fruits and vegetables, demonstrate greater utilization of BFF Centers and community resources, and NFN+ infants would be less likely to have a weight for length greater than the 85^th^ percentile. The study protocol was approved by the Institutional Review Board at Connecticut Children’s Medical Center, was sponsored by the Hartford Childhood Wellness Alliance, and was funded by the National Institutes of Health (NICHD R21 HD073966-A01).

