**Methods/Design:**

Six family centers located in low-income neighborhoods in Hartford, CT were randomized into control and intervention neighborhoods. Fifty-seven mothers were recruited either prenatally or shortly after delivery into the Nurturing Families Network home visitation program; 27 lived in a control neighborhood and received the standard home visitation program and 30 lived in an intervention neighborhood and received both the standard home visitation program and the ECHO intervention. The intervention increases maternal skills in goal-setting, stimulus control and problem-solving, engages family members to support changes, links mothers to neighborhood resources and is embedded in the standard home visitation program. ECHO targets include breastfeeding, solids, juice and sugar-sweetened beverages, routines for sleep and responding to infant cues, television/screen time, and maternal diet and physical activity. We hypothesize that infants in ECHO will have been breastfed longer and exclusively, will have delayed introduction of solids and juice, have longer sleep duration, decreased television/screen time and a lower weight for length *z*-score at 12 months, and their mothers will have greater fruit and vegetable consumption and higher levels of physical activity.

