### Participants

Women who were either prenatal or had just delivered a baby were screened for eligibility for the NFN program using the Revised Early Identification Screening Tool (Reid). The Reid screen consists of 17 items including poverty, unemployment, single head of household, substance abuse, psychiatric care or late prenatal care with a positive Reid screen score being 3 or more affirmative responses. Final eligibility for the NFN Home Visitation Program was determined using results from the Kempe Family Scale which was administered during the first home visit [47, 48] by the NFN Supervisor. Prenatal women enrolled in NFN were further screened for eligibility in ECHO; final determination of eligibility occurred after the birth of the infant. Inclusion criteria for ECHO included singleton birth greater than 34 weeks gestation, any maternal race or ethnicity, no chronic conditions that could affect the growth or development of the infant and residence at the time of the infant’s birth in an ECHO-designated neighborhood. Infants with major malformations, admission to the neonatal intensive care unit or a prolonged hospital stay or infants who were small for gestational age and required special or supplemental nutrition were excluded.

Between November 2013 and December 2014, 117 mothers were screened for enrollment in ECHO and 57 met all initial eligibility criteria, provided consent, and were randomized into either the intervention (n = 30) or control (n = 27) arms (Fig. 2). After the birth of their newborn, 49 dyads continued to meet all final eligibility criteria. Of the 8 dyads that dropped out after providing consent, 2 left the NFN program prenatally, 4 had infants who did not meet eligibility criteria, 1 mother moved out of the area prenatally and 1 mother had special needs that precluded her participation in the study. The demographics of the 49 maternal-infant dyads that met all eligibility criteria are shown in Table 2.

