##### Enhanced support for breastfeeding

NFN+ workers assess the mother’s attitudes and beliefs related to breastfeeding prenatally or in the hospital and provide education about the importance of breastfeeding and its benefits to the infant. After delivery, hospital staff assist new mothers in initiating breastfeeding which the NFN+ worker reinforces and supports in the home. The NFN worker observes the mother breastfeeding with special attention to the mother’s state, infant attachment, positioning, frequency, and duration of feeding. The NFN worker counsels the mother about continuing to breastfeed when returning to work and refers mothers experiencing difficulties to Heritage and Pride, a breastfeeding support program in Hartford [21, 49]. While the decision to breastfeed has often been made prior to enrollment in ECHO, barriers to breastfeeding encountered by Latinas and Blacks (e.g., comfort, lack of social support) are addressed by the NFN+ workers [50].

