### Statistical analysis plan for primary outcomes

The primary outcome measure is the duration and exclusivity of breastfeeding, the time to consumption of SSB/juice and solids, the amount of television/screen time per day, and sleep duration in NFN+ infants as compared to NFN infants. The quality of the randomization and the comparability of the participants have been assessed using >Chi square and t-tests as appropriate (Table 2). Participants were comparable except that intervention participants had higher parity as compared to control participants. Participants are nested and clustered within neighborhoods and these effects are being evaluated and will be controlled for in the statistical analysis. Using an intention to treat and a per protocol analysis, behaviors of NFN+ mothers will be compared to NFN mothers related to SSB/juice consumption (number of ounces per day, age at introduction of SSB/juice; age at beginning solids, duration (weeks) of breastfeeding and sleep duration, soothability, and television viewing hours) using two sample t-tests or Wilcoxon tests. Chi square analysis will be used to compare the proportions of exclusive breastfeeding at 6 months in the two groups. Similarly, we will determine if the intervention decreases the risk that infants would stop exclusive breastfeeding at any time considered in the study. A p ≤ 0.05 will be considered significant.

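### Mothers may enter up to a month after delivery, so breastfeeding stops that precede consent count as outcomes, and the named tests ignore entry time

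*Protocol article*

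**What the plan says.** On entry, Overview and hypotheses invites "Pregnant women or new mothers within one month of delivery who reside in one of six urban neighborhoods". The Abstract describes mothers as "recruited either prenatally or shortly after delivery into the Nurturing Families Network home visitation program", and Participants says "Women who were either prenatal or had just delivered a baby were screened for eligibility for the NFN program". The inclusion and exclusion criteria under Participants do not mention feeding status.

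On the intervention, Enhanced support for breastfeeding has NFN+ workers assess the mother's "attitudes and beliefs related to breastfeeding prenatally or in the hospital and provide education about the importance of breastfeeding". After delivery, hospital staff help with initiation, "which the NFN+ worker reinforces and supports in the home". Observation of feeding, advice on returning to work and referral to a support program follow. The same section concedes: "While the decision to breastfeed has often been made prior to enrollment in ECHO".

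On the analysis, Statistical analysis plan for primary outcomes compares weeks of breastfeeding by t-test or Wilcoxon test and exclusive breastfeeding at 6 months by chi-square. It adds that "we will determine if the intervention decreases the risk that infants would stop exclusive breastfeeding at any time considered in the study". Analyses are by intention to treat and per protocol, and neighborhood clustering is to be controlled for. The section calls the arms comparable except on parity, with reference to Table 2, which has no row for time of entry.

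**The concern.** Three things that the article fixes do not fit together: an entry window that runs to one month after birth, a first breastfeeding step tied to pregnancy or the hospital stay, and endpoints that accumulate from the first days of life. Exclusivity, once lost, can no longer be protected. A mother who consents at three or four weeks may already have given formula or stopped breastfeeding. Her result is then settled on exclusivity, and perhaps on duration, before ECHO reaches her.

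Two consequences follow. The first is dilution, because infants who cannot respond stay in both arms of the comparison. The second is possible confounding. Whole centers were allocated and mothers were recruited within them, so nothing in the design balances prenatal against postnatal entry. If one arm enrolled more of its mothers before birth, the breastfeeding comparison would partly reflect when mothers were recruited. Duration and exclusivity of breastfeeding are named first among the primary outcomes, so the point touches a main result.

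**Working it through.** The plan gives no effect size, control rate or power for breastfeeding. Its power statement concerns SSB/juice and solids, so there is no figure to reproduce here. The check sets the sections side by side and then shows the possible size under stated assumptions.

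**What the text establishes**

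- *Window against component.* A mother first enrolled after discharge cannot receive the early step as described. A mother enrolled in the hospital can. The Training section has study staff supporting consent at the initial home visit, which suggests that some postnatal consents came after discharge; it does not say how many.
- *Window against endpoint.* Weeks of breastfeeding and exclusivity at 6 months necessarily include whatever happened before consent. For the risk of stopping, an infant who stopped before entry is no longer at risk; the article states neither the time origin nor how such infants are counted.
- *Tests.* The t-test, Wilcoxon and chi-square tests have no term for entry time.
- *Balance.* Table 2 shows 21/23 = 91% primiparous in control against 6/26 = 23% in intervention. This does not show that entry time differs, but it shows that center allocation did not balance mothers' characteristics.
- *Split.* Not reported. Of the 8 dyads lost after consent, 2 left NFN prenatally and 1 moved away prenatally, so some mothers entered before birth.

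**Dilution (all inputs assumed)**

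Let *s* be the share entering after birth and *q* the share of those no longer exclusive at consent, equal in both arms. Assume everyone else responds fully.

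Share of effect retained = 1 − *s* × *q*

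- *s* = 0.3, *q* = 0.3: 1 − 0.09 = 0.91
- *s* = 0.5, *q* = 0.5: 1 − 0.25 = 0.75
- *s* = 0.7, *q* = 0.7: 1 − 0.49 = 0.51

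**Confounding with no intervention effect (all inputs assumed)**

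Take exclusivity of 30% in prenatal and 15% in postnatal entrants, with 30% prenatal entry in one arm and 70% in the other.

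- First arm: 0.3 × 0.30 + 0.7 × 0.15 = 0.195
- Second arm: 0.7 × 0.30 + 0.3 × 0.15 = 0.255
- Spurious difference: 0.060

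The difference equals the gap in prenatal share times the gap in exclusivity (0.4 × 0.15 = 0.06). With prenatal shares of 40% and 60% it is 0.2 × 0.15 = 0.03.

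For scale, with 23 and 26 dyads the standard error of the difference is √(0.195 × 0.805/23 + 0.255 × 0.745/26) = √(0.00682 + 0.00731) ≈ 0.119. The 6-point difference is about half a standard error.

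**The case against.** The strongest reply is that intention to treat over all entrants is legitimate. It estimates the effect of the program as offered to women when they join NFN, and if entry timing is balanced, late entry dilutes the estimate without biasing it. Both arms used the same NFN screening, centers were paired, enrollment was sequential, and no imbalance in entry time is shown. This stands, and it is why the all-dyads comparison should remain primary.

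A reader might infer that late entrants miss the breastfeeding intervention altogether. The text does not support that: in-hospital entrants can still have the early step, and support in the home, work counselling and referral remain for those who come later.

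A reader might also infer that the plan analyzes everyone from birth as if equally exposed. No section says so. The origin for the stopping-risk analysis is not stated, intervention dose is recorded, and a per protocol analysis is planned, although none of this is tied to entry time in the article.

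Finally, covariates and time origin are commonly left to a full analysis plan, and their absence from an article is not a fault in itself. The point rests instead on what the article does fix: the window, the timing of the component, the endpoints and named tests that leave entry time out.

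**Conclusion.** The mismatch is real and modest. Breastfeeding stops that precede consent count as outcomes in the duration and 6-month exclusivity comparisons, and the stated tests do not account for when mothers entered. The certain consequence, if any postnatal entrant had already stopped, is dilution. Confounding is possible because centers were randomized, but it is not shown.

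The documents cannot give the size. The 51–91% retained effect and the 3- to 6-point spurious difference rest wholly on assumed inputs, and the 6-point case needs a large imbalance in entry. It would be wrong to read them as estimates for this trial or to conclude that the breastfeeding result is biased. Adjusting for entry time is nevertheless a better method than the tests stated, at almost no cost.

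**What to change.** - Report time of entry (prenatal or after birth) by arm, as a row in Table 2.
- Include it as a fixed covariate in the breastfeeding analyses, using regression counterparts of the t-test and chi-square test that also carry the promised control for neighborhood. Keep the all-dyads intention-to-treat comparison as primary. Entry time is settled at consent, before any ECHO content is delivered to that mother, and follows from consent and birth dates.
- For the risk of stopping exclusive breastfeeding, add a supportive analysis with infant age as the time scale and delayed entry at consent, so that an infant is at risk only if still exclusively breastfed at that point. One age scale for all is preferable to starting some infants at birth and others at consent, because infant age drives stopping. This needs feeding status at entry. The article says questionnaires were completed at the initial home visit but not that they record this, so the analysis is limited to dyads for whom it is available.

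The cost is one degree of freedom in the primary analyses and fewer infants in the supportive analysis only. Recruitment, eligibility and the intervention are untouched.

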### Participants

Women who were either prenatal or had just delivered a baby were screened for eligibility for the NFN program using the Revised Early Identification Screening Tool (Reid). The Reid screen consists of 17 items including poverty, unemployment, single head of household, substance abuse, psychiatric care or late prenatal care with a positive Reid screen score being 3 or more affirmative responses. Final eligibility for the NFN Home Visitation Program was determined using results from the Kempe Family Scale which was administered during the first home visit [47, 48] by the NFN Supervisor. Prenatal women enrolled in NFN were further screened for eligibility in ECHO; final determination of eligibility occurred after the birth of the infant. Inclusion criteria for ECHO included singleton birth greater than 34 weeks gestation, any maternal race or ethnicity, no chronic conditions that could affect the growth or development of the infant and residence at the time of the infant’s birth in an ECHO-designated neighborhood. Infants with major malformations, admission to the neonatal intensive care unit or a prolonged hospital stay or infants who were small for gestational age and required special or supplemental nutrition were excluded.

Between November 2013 and December 2014, 117 mothers were screened for enrollment in ECHO and 57 met all initial eligibility criteria, provided consent, and were randomized into either the intervention (n = 30) or control (n = 27) arms (Fig. 2). After the birth of their newborn, 49 dyads continued to meet all final eligibility criteria. Of the 8 dyads that dropped out after providing consent, 2 left the NFN program prenatally, 4 had infants who did not meet eligibility criteria, 1 mother moved out of the area prenatally and 1 mother had special needs that precluded her participation in the study. The demographics of the 49 maternal-infant dyads that met all eligibility criteria are shown in Table 2.

**Fig. 2 Fig2:**
[figure not shown]
Study recruitment

**Table 2 Tab2:** Demographics of mother infant dyads

	Control (n = 23) (%)	Intervention (n = 26) (%)
Maternal age yrs (mean ± SD)	22.05 ± 5.73	24.35 ± 5.37
<18 years	2 (9 %)	1 (4 %)
18–30 years	18 (78 %)	21 (81 %)
>30 years	1 (4 %)	4 (15 %)
Parity (Primip) (%)*	21 (91 %)	6 (23 %)
Income	8 (35 %)	12 (46 %)
< $15,000	2 (9 %)	3 (12 %)
$15,000-$30,000	1 (4 %)	4 (15 %)
$30,000-$50,000	0 (0 %)	1 (4 %)
>$50,000	8 (35 %)	5 (19 %)
Do not know		
Race/Ethnicity	6 (25 %)	7 (27 %)
African American/Black	12 (52 %)	17 (65 %)
Hispanic	4 (17 %)	2 (8 %)
Other		
Marital Status: Married	3 (13 %)	7 (27 %)
Education	8 (35 %)	11 (42 %)
<12^th^ grade	6 (26 %)	5 (19 %)
High school or GED	7 (30 %)	7 (27 %)
>High school or GED		
Employment: Yes	8 (35 %)	10 (38 %)
Language spoken: English	21 (92 %)	18 (69 %)
Place of birth: United States	13 (58 %)	8 (31 %)
Public insurance	12 (52 %)	12 (46 %)
Maternal smoking (Yes, %)	5 (22 %)	6 (23 %)
Infant birth weight (Lbs) (Mean ± SD)	7.37 ± 0.83	7.36 ± 1.08
Infant sex (M, %)	12 (52)	9 (35)

Expressed as n (%) except as noted. Percentages may not add to 100 % due to rounding and missing data

*p < 0.001. All other differences were not significant

### Interventions

#### Intervention components common to NFN and NFN+ participants

Mothers who agreed to participate in the NFN program and then were eligible for ECHO and provided consent received a weekly home visit by the NFN home visitor. At the first home visit, the NFN Supervisor assessed the family’s strengths and needs using the 10-item Family Stress Scale (Kempe Scale) and tailored the NFN program using the PAT and Partners curricula (standard current practice). These curricula were then administered by home visitors. Visit documentation is kept through content logs which include information both about the visit frequency and the content of the material presented/discussed during the visit.

#### Intervention components unique to NFN+

Intervention components unique to NFN+ include: 1) enhanced support regarding breastfeeding, 2) creation of a Family Wellness Plan that teaches mothers goal-setting and self-monitoring skills to assess her family’s progress, 3) education and skill-building in behavioral strategies (problem-solving and stimulus control) to implement desired changes in four infant target areas (breastfeeding, SSB/juice consumption, introduction of solids, television/screen time and infant routines), 4) a toolkit with items useful to support the changes, and 5) linkages to community programs that support healthy behavior change.

##### Enhanced support for breastfeeding

NFN+ workers assess the mother’s attitudes and beliefs related to breastfeeding prenatally or in the hospital and provide education about the importance of breastfeeding and its benefits to the infant. After delivery, hospital staff assist new mothers in initiating breastfeeding which the NFN+ worker reinforces and supports in the home. The NFN worker observes the mother breastfeeding with special attention to the mother’s state, infant attachment, positioning, frequency, and duration of feeding. The NFN worker counsels the mother about continuing to breastfeed when returning to work and refers mothers experiencing difficulties to Heritage and Pride, a breastfeeding support program in Hartford [21, 49]. While the decision to breastfeed has often been made prior to enrollment in ECHO, barriers to breastfeeding encountered by Latinas and Blacks (e.g., comfort, lack of social support) are addressed by the NFN+ workers [50].

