### Training

#### Training common to NFN and NFN+

All NFN and NFN+ Supervisors received training in the ethical conduct of human research and are certified. Additionally, they received two hours of training in how to obtain consent for the ECHO study and in how to complete each of the program’s questionnaires. Study staff accompanied the supervisors during the initial home visit to support the supervisors in obtaining consent and in completing the questionnaires.

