#### Process or intermediary variables

Message-specific maternal knowledge, intention and self-efficacy is being assessed using the Infant Feeding Practice Survey II [60, 61] adapted for prenatal and postnatal feeding practices and the Infant Feeding Style Questionnaire [62].

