### Evaluation plan

Assessments will occur at birth and when the infant is 6 and 12 months. The Family Wellness Plan book is collected at 6 and 12 months and copied and returned to the family. Primary outcomes will be the child’s targeted behaviors at 12 months (i.e., extent and duration of breastfeeding, SSB consumption, timing of introduction of solids, sleep duration and soothability and television viewing) (Fig. 3). Assessed process variables include changes in mothers’ knowledge about dietary recommendations, intentions to make these changes, and self-efficacy to make healthy choices. Six month intermediary variables include changes in the home food environment and mothers’ shopping and cooking practices, child feeding styles, maternal stress, positive parenting practices, and community resource utilization. The RE-AIM analytic framework will be used [72, 73]. For RE-AIM, Reach will be explored by determining the percent of mothers/infants who were excluded and the reasons for exclusion, the percent of eligible mothers/infants who participated, and reasons for dropping out. Effectiveness will be evaluated by comparing differences in maternal behaviors at 6 months between control and intervention mothers and short-term attrition. For Adoption, intervention use (number of doses of each intervention and number of intervention types rendered) and NFN+ worker satisfaction and intention to use the intervention after study’s end will be evaluated. Implementation will be evaluated using the number of completed home visits and the association between these indicators and maternal behaviors. Maintenance will be assessed by examining child behaviors and weight for length *z*-scores at 12 months.

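### Breastfeeding, a primary outcome, is compared with tests that take no covariates, although feeding intention appears to be recorded at the initial visit and could be adjusted for

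*Protocol article*

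**What the plan says.** All references are to the protocol article.

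- *Enhanced support for breastfeeding* notes: "While the decision to breastfeed has often been made prior to enrollment in ECHO". The same sentence goes on to say that NFN+ workers address barriers to breastfeeding.
- *Process or intermediary variables*: "Message-specific maternal knowledge, intention and self-efficacy is being assessed using the Infant Feeding Practice Survey II", an instrument "adapted for prenatal and postnatal feeding practices". The section is not limited to one arm; measures taken only in the intervention arm have their own section.
- *Training common to NFN and NFN+*: study staff went with supervisors to the initial home visit to help "in obtaining consent and in completing the questionnaires".
- *Evaluation plan*: "Assessments will occur at birth and when the infant is 6 and 12 months". Process variables are changes in knowledge, "intentions to make these changes, and self-efficacy to make healthy choices".
- *Statistical analysis plan for primary outcomes*: "The primary outcome measure is the duration and exclusivity of breastfeeding", followed by the other infant behaviors. Duration is compared by t-test or Wilcoxon test. For exclusivity, "Chi square analysis will be used to compare the proportions of exclusive breastfeeding at 6 months in the two groups". The risk of stopping exclusive breastfeeding is also to be examined, with no method named. Neighborhood clustering is the only factor to be controlled for.

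**The concern.** Breastfeeding duration and exclusivity have no baseline value of their own. The nearest substitute is what the mother intended before the program reached her, and the article itself says that the choice to breastfeed often predates enrollment. It gives intention only one role, as a process variable.

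Balance on intention cannot be taken for granted. Six centers were randomized, three per arm, and a mother's arm followed from the neighborhood in which she was recruited. If the arms differ in prior intention, an unadjusted comparison carries part of that difference into the estimated effect. Even if they do not differ, variation between mothers that intention could explain stays in the standard error of a small trial.

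**Working it through.** **The plan's own figure.** There is none on this point. The only power statement concerns juice and solids, not breastfeeding, and is not used here.

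**Is there a baseline value of intention?** No sentence says so outright. Three places point to it:
- the instrument has a prenatal form;
- questionnaires are completed at the initial visit, under training common to both arms;
- the Evaluation plan analyses changes in intention, which need a starting value.

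The inference is reasonable but not certain. The scheduled assessments begin at birth, and it is not stated which questionnaires were completed at the initial visit.

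**Inputs.**
- Dyads meeting final eligibility: 23 control, 26 intervention (Table 2).
- Centers: 6, so 49/6 = 8.2 dyads per center on average.
- Correlation r of intention with duration: assumed, 0.3 to 0.6.
- Intracluster correlation (ICC) of intention: assumed, 0 to 0.10.

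**Precision.** Adjusting for a covariate with correlation r multiplies the standard error by √(1 − r²). The equivalent increase in sample size is 1/(1 − r²).

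| r (assumed) | SE ratio | Equivalent sample size |
|---|---|---|
| 0.3 | √0.91 = 0.95 | 1/0.91 = 1.10 |
| 0.5 | √0.75 = 0.87 | 1/0.75 = 1.33 |
| 0.6 | √0.64 = 0.80 | 1/0.64 = 1.56 |

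The unadjusted detectable difference in duration (two-sided 0.05, 80% power) is (1.96 + 0.84) × √(1/23 + 1/26) = 2.80 × 0.286 = 0.80 SD. Adjusted, it is 0.77 SD at r = 0.3, 0.70 SD at r = 0.5 and 0.64 SD at r = 0.6. These figures ignore clustering.

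**Cost of the extra terms.** Adding q terms inflates the variance by roughly (N − 3)/(N − 3 − q). For two terms and N = 49 this is 46/44 = 1.045. At r = 0.3 the net variance ratio is 0.91 × 1.045 = 0.95. At r = 0.2 it is 0.96 × 1.045 = 1.00, which is no gain.

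**Exposure to imbalance.** The difference between arms in mean intention that chance alone produces has a standard deviation of √[(1/23 + 1/26) × (1 + 7.17 × ICC)], where 7.17 is 49/6 − 1.
- ICC 0: 0.286 SD.
- ICC 0.10: 0.286 × √1.717 = 0.375 SD.

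An unadjusted test passes r times the realized difference into the estimate. At r = 0.5, a difference of one such standard deviation shifts it by 0.5 × 0.286 = 0.14 SD to 0.5 × 0.375 = 0.19 SD.

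**Did baseline differences occur?** Nothing is reported on intention. Parity shows that large ones could: 21/23 = 91% primiparous in control against 6/26 = 23% in intervention, p < 0.001 in Table 2.

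**The case against.** The other side has real strength on five points.

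1. **The remark on prior decisions is limited.** A reader might infer that the prior decision largely fixes how long and how exclusively a mother breastfeeds. The text does not support that. It speaks of the decision to breastfeed, says only that it is often already made, and goes on to barriers that the program addresses. The correlation is therefore unknown. This stands.
2. **The baseline value is inferred.** A reader might conclude that usable data are in hand for every mother. The article does not establish this. Mothers could also enroll up to a month after delivery, when feeding has begun and intention means something different. This stands, and it shapes the fix.
3. **Adjustment could do harm.** NFN+ workers educate mothers about breastfeeding before delivery or during the hospital stay. Intention recorded after that contact may be part of how the intervention works, and adjusting for it would remove some of the effect. This also stands, so the birth assessment is not a safe baseline.
4. **Covariates are often left to an unseen analysis plan, and clustering control implies some model.** This stands only in part. The article has its own analysis section, names the tests there and names what will be controlled for, so the point concerns a stated choice. The promised clustering control does make adding a covariate easy.
5. **The imbalance actually documented is in parity, not intention.** That is true. Parity is cited here only to show that balance is not assured, and adjusting for intention does not settle how parity should be handled.

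**Conclusion.** The concern holds in a limited form. The stated tests for breastfeeding duration and exclusivity leave out a baseline measure that the article implies is collected. The cost is lost precision and exposure to any imbalance in intention that happened to arise.

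A reader might go further and call the unadjusted effect biased. The documents do not support that: chance imbalance averages to zero under randomization and is covered by a correctly computed standard error. Only differential recruitment between arms would bias the estimate, and no evidence of that in intention is given.

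The size rests on an assumed correlation. The standard error would fall by about 5% at r = 0.3 and 20% at r = 0.6, before the small cost of the added terms and ignoring clustering. At r near 0.2 there is nothing to gain. The point is a worthwhile improvement at little cost, not an error that invalidates the comparison.

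**What to change.** - Pre-specify regression models for breastfeeding duration and for exclusivity at 6 months, with the clustering control already promised. Include feeding intention as recorded at the consent or initial visit, before any NFN+ breastfeeding education. Use the same covariates in the analysis of time to stopping exclusive breastfeeding.
- Add an indicator for prenatal versus postnatal enrollment, because intention does not mean the same thing before and after feeding has begun.
- State which questionnaire and which visit supply the covariate.
- Use later intention values only as process outcomes. Where no value before NFN+ contact exists, treat it as a missing baseline covariate and do not substitute the birth or a later value.

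The cost is one or two model terms with 49 dyads, and the gain is small if the correlation is low. If the baseline value was recorded as the article implies, no new data are needed. That should be confirmed first.
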